### Safety Analysis

Safety analysis will be performed on all subjects enrolled in the study with a follow-up safety assessment. Adverse event data will be listed individually and summarized by system organ class and preferred terms within a system organ class. The number and percentage of subjects with adverse events (AEs), serious adverse events (SAEs), AEs that lead to discontinuation, study device-related AEs (determined by investigator), and AEs that lead to death will be summarized. Only AEs grade 2 or higher will be presented. When calculating the incidence of adverse events, each adverse event will be counted only once for a given subject. If the same adverse event occurs on multiple occasions in a subject, the occurrence with the highest severity and relationship to study device will be reported. If two or more adverse events are reported as a unit, the individual terms will be reported as separate events. AEs will also be summarized with regards to severity and relation to study drug. Additionally, the frequency of each AE within-subject will be calculated and summarized across all subjects in order to rank the commonality of each particular AE.

Vital signs, hematology, and clinical chemistry parameters from baseline to the end of the study will be presented as outlined above for continuous outcomes and reported to the DSMB at the regularly scheduled meetings. Incidence of changes in laboratory parameters from normal to abnormal, based on Boston Children’s Hospital reference ranges, will be identified and lab values listed by subject.

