| **Statistical methods**  Data will be summarized in tables listing the number of subjects, mean, standard deviation, standard error, 95% confidence interval (CI), median, interquartile range (IQR), minimum, and maximum for continuous data and number of subjects, frequency and percentage for categorical data. Summaries will be presented by subject and visit, as well as in aggregate when appropriate. All statistical analyses will be performed with SAS version 9.4 or later (Cary NC). | |
| Assessment of change in continuous outcomes will be made using the area under the curve, adjusted for baseline, calculated over study day 7 to 90 (AUC_7-90_). Adjustment for baseline will be made by dividing the outcome value at each visit by the baseline value, leading to interpretation of AUC_7-90_ as a mean relative percent increase or decrease in outcome depending on whether AUC_7-90_ is greater or less than unity (1), respectively. The assumption of normality will be assessed for AUC_7-90_ for each continuous outcome using quantile-quantile (Q-Q) plots and the Shapiro-Wilk test. Outcomes determined to be skewed will be normalized using an appropriate transformation (e.g. logarithm; normal scores based on ranks).  Adverse event data will be listed individually and summarized by system organ class and preferred terms within a system organ class. The adverse events will be recorded by the study nurse and/ or study physician and classified using the *Common Terminology Criteria for Adverse Events Version 5.0.* The number and percentage of subjects with grade 2 or higher adverse events (AEs), serious adverse events (SAEs), AEs that lead to discontinuation, study device-related AEs (determined by investigator), and AEs that lead to death will be summarized. Vital signs, hematology, and clinical chemistry parameters from baseline to the end of the study will be presented as outlined above for continuous outcomes and reported to the DSMB at the regularly scheduled meetings. Incidence of changes in laboratory parameters from normal to abnormal, based on Boston Children’s Hospital reference ranges, will be identified and lab values listed by subject. | |

TABLE OF CONTENTS

Page

[STUDY SYNOPSIS 3](#_Toc126862688)

[LIST OF TABLES 15](#_Toc126862689)

[LIST OF FIGURES 15](#_Toc126862690)

[LIST OF ABBREVIATIONS 16](#_Toc126862691)

[1.0 INTRODUCTION 17](#_Toc126862692)

[1.1 BACKGROUND 17](#_Toc126862693)

[1.2 STUDY RATIONALE 21](#_Toc126862694)

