### Safety endpoints

The safety endpoints include:

- Subject incidence of adverse events, including changes in stool consistency assessed by Bristol scale, changes in stool amount/frequency (if applicable), increased ostomy output (if applicable, defined as >2.5 mL/kg/hour), the need to decrease enteral feeds, changes in urine color assessed by Dehydration Color scale, and discontinuation from the study treatment.
- Subject incidence of abnormalities in vital signs, assessed at baseline, Day 7, 14, 28, 60, and 90.
- Subject incidence of abnormalities in hematology and biochemistry parameters assessed at baseline, Day 7, 14, 28, 60, and 90.

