# PROCEDURES FOR HANDLING ADVERSE EVENTS AND SERIOUS ADVERSE EVENTS

## DEFINITION OF AN ADVERSE EVENT

The following definition of adverse event (AE) will be used for this study:

- Adverse event means any untoward medical occurrence associated with the use of a device in humans, whether or not considered device-related.
- All AE’s post-baseline will be captured. Adverse events grade 2 or higher will be analyzed.

An adverse event can be any unfavorable and unintended sign (including an abnormal laboratory finding), symptom, or disease (new or exacerbated) temporally associated with the use of the investigational product, regardless of whether it is considered to be related to the investigational product.

Examples of AEs include the following:

- Significant or unexpected worsening or exacerbation of the indication under study
- Exacerbation of a chronic or intermittent preexisting condition including an increase in frequency or intensity of the condition
- New conditions detected or diagnosed after investigational product administration even if they were present before the start of the study
- Signs, symptoms, or the clinical sequelae of a suspected interaction with another medical product
- Signs, symptoms or the clinical sequelae of a suspected overdose of either investigational product or a concurrent medication

Overdose will not be reported as an AE or serious adverse event (SAE), but rather the symptoms resulting from the overdose.

Examples of AEs do not include the following:

- Situations that are unwanted by the subject but in which an untoward medical occurrence did not occur, for example social inconvenience after admission to a hospital
- Anticipated day-to-day fluctuations of a preexisting disease or condition (present or detected before enrollment) that does not worsen overall
- Expected progression of the disease being studied, including signs or symptoms of the disease, unless progression is more severe than expected for the subject’s condition
- The Common Terminology Criteria for Adverse Events (CTCAE) version 5 (https://ctep.cancer.gov/protocoldevelopment/electronic_applications/docs/CTCAE_v5_Quick_Reference_5x7.pdf) will be used to grade toxicities.

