## DEFINITION OF A SERIOUS ADVERSE EVENT

In this clinical trial, a serious adverse event is defined as an AE that meets any of the following criteria:

- Results in death
- Is life-threatening

The term life-threatening in the definition of an SAE refers to an event in which the subject was at risk of death at the time of the event. Life‑threatening does not refer to an event that hypothetically might have caused death if it were more severe.

- Requires hospitalization or a prolongation of an existing hospitalization

In general, hospitalization signifies that the subject has been detained at the hospital or emergency ward for observation or treatment that would not have been appropriate in the physician’s office or out-patient setting. Complications that occur during hospitalization are AEs, but not necessarily SAEs. An occurrence or complication that prolongs hospitalization is an SAE. When there is doubt as to whether hospitalization occurred or was necessary, the AE will be considered an SAE. Hospitalization for elective treatments of a preexisting condition that did not worsen from its original baseline level is not considered an SAE.

- A persistent or significant incapacity or substantial disruption of the ability to conduct normal life functions

This definition is not intended to include AEs of relatively minor medical significance such as uncomplicated headache, nausea, vomiting, diarrhea that may interfere or prevent everyday life functions but do not constitute a substantial disruption.

- Other important medical event

Medical or scientific judgment will be exercised in deciding whether reporting is appropriate for other important medical events that may not result in death, be life-threatening, or require hospitalization but still may jeopardize the subject or may require medical intervention to prevent one of the outcomes listed in this definition. These events will also be considered serious. Examples of such events are intensive treatment in an emergency room or at home for allergic bronchospasm, blood dyscrasias or convulsions that do not result in hospitalization, or development of drug dependency or drug abuse.

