## ASSESSMENT OF INTENSITY

The investigator will assess the intensity for each AE and SAE reported during the study. The assessment will be based on the investigator’s clinical judgment.

The classifications in Table 6 will be used in assigning intensity of each AE recorded in the case report form. The Common Terminology Criteria for Adverse Events (CTCAE) version 5.0 will be used to grade toxicities. (https://ctep.cancer.gov/protocolDevelopment/electronic_applications/ctc.htm)

Table 6. Classification of AEs by Intensity

| **Intensity** ^a^ | **Definition** |
| --- | --- |
| Mild AE (Grade 1) | An event that is easily tolerated by the subject, causing minimal discomfort and not interfering with everyday activities. |
| Moderate AE (Grade 2) | An event that is sufficiently discomforting to the extent of interfering with normal everyday activities. |
| Severe AE (Grade 3) | An event that prevents the subject from performing normal everyday activities. |
| Life-threatening or disabling AE (Grade 4) | An event that, at the time of occurrence, put the subject at risk of death or resulted in a persistent or significant disability or incapacity |
| Death related to AE  (Grade 5) | An event that resulted in death |

AE = adverse event

a From Common Terminology Criteria for Adverse Events (https://ctep.cancer.gov/protocolDevelopment/electronic_applications/ctc.htm)

Any AE that changes in intensity or grade during its course will be recorded in the CRF at the highest-level experience by the subject during a single course.

An AE that is assessed as severe should not be confused with an SAE. Severity is a category used for rating the intensity of an AE (such as mild, moderate, or severe myocardial infarction). However, the event itself may be of relatively minor medical significance, such as a severe headache. Both AEs and SAEs can be assessed as severe. An AE is defined as serious when it meets one of the pre‑defined outcomes as described in Section 9.2.

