## LIVER EVENTS

When either serum alanine aminotransferase (ALT) or serum aspartate aminotransferase (AST) levels exceed three times higher than values recorded at screening, serum ALT, AST, alkaline phosphatase, and total bilirubin will be repeated within 48 to 72 hours. Alcresta will be notified, and liver event pages of the case report form will be completed. If the ALT or AST remain more than three times the values recorded at screening, or total bilirubin remains greater than two times ULN, then repeat liver enzymes will be obtained every 3 days and the appropriate case report form page will be completed with available history of symptoms and other assessments (e.g., ultrasound or computerized tomography of the liver and tests for hepatitis).

Investigational product use will stop if one of the following occurs:

- ALT or AST exceed eight times the values recorded at screening.
- ALT or AST exceed five times the values recorded at screening for more than 2 weeks.
- ALT or AST exceed three times the values recorded at screening and total bilirubin exceeds two times ULN or international normalized ratio exceeds 1.5.
- ALT or AST exceed three times the values recorded at screening, with the appearance of fatigue, nausea, vomiting, right upper quadrant pain or tenderness, fever, rash, or eosinophilia (>5%).
- Monitoring will be continued until abnormalities return to reference range or baseline levels.

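### The grade 2 filter covers every safety count, so mild-graded serious, device-related and device-stopping events are left out of the final tables

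*Protocol*

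**What the plan says.** Section 10.2.3 (Safety Analysis) first names the categories to be counted. Besides AEs overall these are "serious adverse events (SAEs), AEs that lead to discontinuation, study device-related AEs (determined by investigator), and AEs that lead to death will be summarized". The next sentence is "Only AEs grade 2 or higher will be presented". No category is exempt. Section 9.1 says that all post-baseline AEs are captured, but then "Adverse events grade 2 or higher will be analyzed".

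Other places bear on the same tables:

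- **Section 3.3.3 (Safety endpoints)** sets no grade limit: "Subject incidence of adverse events, including changes in stool consistency assessed by Bristol scale". Its list of AEs includes stopping study treatment.
- **The synopsis** sets the grade 2 threshold for AE incidence in its objectives and outcomes. Its statistical methods read "The number and percentage of subjects with grade 2 or higher adverse events (AEs), serious adverse events (SAEs), AEs that lead to discontinuation", followed by device-related AEs and deaths.
- **Section 10.2.4 (Other considerations)** makes the safety population a subset of the full-analysis population: treated subjects who also had an AE of at least grade 2. Section 10.2.3 instead uses every enrolled subject with a follow-up safety assessment.

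**The concern.** Grade measures how intense an event is. SAE, device-related and discontinuation counts measure its consequence or cause. They are tabulated separately because an event can matter on these grounds while being mild. A grade filter placed over them removes the cases that intensity does not pick up.

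Safety and tolerability are stated objectives of this single-arm pediatric study. With no control group, the absolute counts in these tables are the safety result. A filter that can only lower them gives a more favourable picture of tolerability than the collected data support. Mild device-related events are probably the largest group affected, because the signals the protocol names, such as changes in stool consistency or urine colour, can be mild.

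**Working it through.** The protocol states no figure for the effect of the filter, so there is none to reproduce. The check has three parts.

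**1. Can a grade 1 event fall into these categories under the protocol's own rules?**

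- *Grade 1* (section 9.5, Table 6): "An event that is easily tolerated by the subject, causing minimal discomfort and not interfering with everyday activities".
- *Serious.* Section 9.5 warns against confusing severity with seriousness, and seriousness is defined by outcome in section 9.2. That section adds "When there is doubt as to whether hospitalization occurred or was necessary, the AE will be considered an SAE". Nothing there depends on grade.
- *Device stopped.* Section 9.1 takes a child off the device after an allergic or anaphylactic reaction and names no minimum grade.
- *Discontinued.* Section 9.12 removes a child from the study if an AE leads to a feed being withheld beyond 24 hours, again with no grade condition.
- *Device-related.* Section 9.6 assigns causality to every AE, whatever its grade.
- *Death.* Always grade 5 in Table 6, so unaffected.

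So all the categories except death can contain grade 1 events. The omission is confined to events that never rise above grade 1, because sections 9.5 and 10.2.3 record the highest severity reached.

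**2. What happens to such a child in the tables?**

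| Rule applied | Grade 1 SAE, device-related AE or device stop |
|---|---|
| 10.2.3 as written | Removed from the numerator, kept in the denominator |
| 10.2.4 safety population | If it is the child's only event, the child leaves the denominator too |
| 10.2.3 corrected, 10.2.4 unchanged | If it is the child's only event, still excluded |

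The third row shows that changing 10.2.3 and 9.1 alone is not enough. Under the 10.2.4 definition, moreover, every member of the safety population has a grade 2 or higher AE, so the overall incidence of such events would be 100% by construction.

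**3. Size.** The denominator is n = 32 (section 3.2), assuming every subject has a follow-up safety assessment. One omitted child is 1/32 = 3.1 percentage points. The protocol gives no rate, so the numbers of children below are assumptions, shown only for scale. Intervals are exact (Clopper-Pearson).

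| Children whose only device-related events are grade 1 (assumed) | Share missing from the table | Exact 95% CI |
|---|---|---|
| 0 | 0/32 = 0% | 0 to 10.9% |
| 1 | 1/32 = 3.1% | 0.1 to 16.2% |
| 2 | 2/32 = 6.3% | 0.8 to 20.8% |
| 4 | 4/32 = 12.5% | 3.5 to 29.0% |

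If no other child had a device-related event, the filtered table would show the first row in every case.

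The chance that at least one of 32 children has such an event is 1 − (1 − p)^32. For assumed p = 2%, 5% and 10% this gives 48%, 81% and 97%.

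**The case against.** The strongest reply is that the grade 2 threshold was chosen in advance, is repeated across the protocol, and hides nothing from oversight. Much of that stands. Section 9.1 captures all AEs and puts all of them in the annual report. Section 9.8 sends every SAE to the IRB and DSMB whatever its grade. Section 10.2.3 lists laboratory values by subject where they move from normal to abnormal. Grade 1 SAEs are also likely to be few, since a hospital stay usually interferes with daily life. None of this puts the omitted events back into the SAE, device-related and discontinuation counts, and the protocol gives no reason for applying the threshold there.

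Three stronger readings are tempting but not supported:

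- *A symptom-free child stopped under section 9.10 because "ALT or AST exceed eight times the values recorded at screening" is grade 1 and disappears.* That follows only if Table 6 alone decides the grade. The synopsis and sections 9.1 and 9.5 name CTCAE version 5 for classifying or grading events, and its laboratory thresholds are not in the documents. Section 9.10 also provides dedicated liver-event CRF pages.
- *The synopsis contradicts 10.2.3.* The words grade 2 or higher stand before the first item of its list and can be read as governing only that item or all of them. The synopsis is ambiguous and needs aligning, but it does not prove a conflict.
- *These events are counted as zero, or a particular percentage is hidden.* They are left out of the final tables, not lost from the data, and no document says how many there would be.

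**Conclusion.** The point holds as a fault in a stated presentation rule. Sections 10.2.3 and 9.1 extend a threshold suited to overall AE incidence to SAEs, device-related AEs and AEs leading to discontinuation, where the protocol's own definitions do not depend on grade. Followed literally, the numerators in those categories can only be too low, by 3.1 points per omitted child on a denominator of 32. How many children that means is unknown.

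The conclusion rests on the plain wording of 10.2.3 and 9.1 and on taking 32 as the denominator. If the 10.2.4 population is used instead, the denominator is smaller and unknown. The numerators are still too low, but the percentages can then move in either direction. That is a further reason to settle the population in the same amendment.

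**What to change.** - **Sections 9.1 and 10.2.3:** keep the grade 2 or higher limit for the overall AE incidence table only. State that SAEs, device-related AEs and AEs leading to discontinuation or device stop are analysed and presented at any grade. A device stop then appears in the tables whichever grading scheme was applied to it.
- **Synopsis, Statistical methods:** reword the list so that the grade limit clearly attaches to overall AE incidence alone.
- **Section 10.2.4:** define the safety population by exposure to the device, without requiring an AE of any grade, and reconcile it with the population named in 10.2.3. Without this step, a child whose only event is a grade 1 SAE or device-related event stays excluded.

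The cost is a few sentences, and safety tables that are slightly longer and slightly less favourable. All AEs are already collected, so no new data are needed, and no clinical rule changes.

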| **Criteria for evaluation:**  Treatment will be initiated on study Day 1.  Primary outcome:   - The change from baseline in PN calories, assessed weekly throughout the study.   Secondary outcome:   - The change from baseline in body weight (weight-for-age z-score), assessed weekly throughout the study.   Safety outcomes:   - The incidence of adverse events, grade 2 or higher. All adverse events will be reported by study participants including changes in stool consistency (Bristol scale)/amount/frequency (if applicable), increased ostomy output (if applicable, defined as >2.5 mL/kg/hour), the need to decrease enteral feeds, changes in urine color assessed by Dehydration Color scale and discontinuation from the study treatment, assessed over the entire study from baseline until Day 90. - The incidence of abnormalities in vital signs (blood pressure, pulse rate, respiratory rate, temperature) assessed at baseline, Day 7, 14, 28, 60, and 90. - The incidence of abnormalities in hematology and biochemistry parameters, based on Boston Children’s Hospital reference ranges, assessed at baseline, Day 7, 14, 28, 60, and 90.   Exploratory outcomes:   - The change from baseline in 72-hour fecal fat and coefficient of fat absorption, assessed at baseline (Days -3 to -1) and prior to the end of the study (Days 87-89). - The change from baseline in plasma fatty acid composition and fat-soluble vitamins (A, D, E, and K), assessed at Day 7, 14, 28, 60, and 90. - Change in growth height (assessed by height-for-age Z-score) and head circumference (assessed by head-circumference-for-age z-score) [in subjects < 36 months]) from baseline, assessed at Day 7, Day 14, Day 28, Day 60, and Day 90 - The change in BMI z-score assessed at Day 7, 14, 28, 60, and 90. - The change from baseline in PN volume, assessed weekly. - The change from baseline in total enteral calories and total enteral volume, assessed weekly. - The change from baseline in total oral calories and total oral volume, assessed weekly. - The ability to wean from PN, assessed over the entire study from baseline until Day 90. | |

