## STATISTICAL ANALYSIS

### General Overview

Data will be summarized in tables listing the number of subjects, mean, standard deviation, standard error, 95% confidence interval (CI), median, interquartile range (IQR), minimum, and maximum for continuous data and number of subjects, frequency and percentage for categorical data. Summaries will be presented by subject and visit, as well as in aggregate when appropriate. Outcomes will be presented in their native units (i.e. as collected), in addition to transformed units when necessary (for example logarithmic). Anthropometry outcomes (weight, height, head circumference, weight-for-height, body mass index) will be examined as z-scores using the Centers for Disease Control growth charts. All outcomes will be explored visually using various graphing methods, including (but not limited to) box-whisker, profile, and bar plots. All statistical analyses will be performed with SAS version 9.4 or later (Cary NC).

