### Outcomes Evaluation

Continuous outcomes, which include all outcomes except the incidence of adverse events (AEs) and incidence of weaning from PN, will be described as indicated in the general overview above using summary measures at each visit. Incidence of ever weaning from PN will be summarized by frequency count and percentage. Analysis for incidence of AEs grade 2 or higher is described in the Safety Analysis section below.

Assessment of change in continuous outcomes will be made using the area under the curve between study day 7 and 90 (AUC_7-90_), adjusted for baseline, calculated over all relevant assessment timepoints (5 and 13 post-baseline weekly assessments for measurements obtained in clinic and at home, respectively). Measurements obtained in clinic will be assessed at study days 7, 14, 28, 60 and 90, while those obtained at home will be assessed on study days 7, 14, 21, 28, 35, 42, 49, 56, 63, 70, 77, 84, 90.

Adjustment for baseline will be made by dividing the outcome value at each assessment by the baseline value, leading to interpretation of AUC_7-90_ as a mean relative percent increase or decrease in outcome depending on whether AUC_7-90_ is greater or less than unity (1), respectively. AUC_7-90_ will be calculated as a time-weighted average, given by the equation:

$$\frac{0.5\cdot\sum\left( t_{i+1}-t_{i} \right)\left( r_{i}+r_{i+1} \right)}{\sum\left( t_{i+1}-t_{i} \right)}$$

where $t_{i}$ denotes the assessment day as described above,, and $r_{i}= y_{i}/y_{1}$ denotes the outcome at assessment day $t_{i}$ divided by the baseline (day 1) value. Hypothetical examples for a single subject with reduction in outcome at each visit is shown below in Figure 3 for measurements obtained in clinic (a) and measurements obtained at home (b). The dotted lines enclose a reference AUC_7-90_=1 (indicating no change in outcome), and the gray shaded area indicates AUC_7-90_.

Figure 3. Hypothetical examples of area under the curve for one subject

| [figure not shown] | [figure not shown] |
| --- | --- |
| a. Example of in-clinic outcome assessment. | b. Example of at-home outcome assessment. |

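### The vital-sign safety endpoint is a count of children with abnormal values, but section 10.2.3 plans only a continuous-outcome presentation for vital signs and gives the abnormality count to laboratory values alone

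*Protocol*

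**What the plan says.** Section 3.3.3 of the protocol lists this safety endpoint: "Subject incidence of abnormalities in vital signs, assessed at baseline, Day 7, 14, 28, 60, and 90". The synopsis, under Criteria for evaluation, says the same and names the four signs: "The incidence of abnormalities in vital signs (blood pressure, pulse rate, respiratory rate, temperature) assessed at baseline, Day 7, 14, 28, 60, and 90". Both describe a count of children, not a mean level.

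The analysis is in section 10.2.3: "Vital signs, hematology, and clinical chemistry parameters from baseline to the end of the study will be presented as outlined above for continuous outcomes". The synopsis repeats this under Statistical methods. Section 10.2.2 defines the class: "Continuous outcomes, which include all outcomes except the incidence of adverse events (AEs) and incidence of weaning from PN". Outcomes in that class are summarised at each visit, and their change is assessed by AUC7-90, a time-weighted average of ratios. For that average, "Adjustment for baseline will be made by dividing the outcome value at each assessment by the baseline value", and "Measurements obtained in clinic will be assessed at study days 7, 14, 28, 60 and 90". Section 10.2.1 adds minimum and maximum to the summaries and says: "Summaries will be presented by subject and visit, as well as in aggregate when appropriate".

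Section 10.2.3 then provides a count, for laboratory values only: "Incidence of changes in laboratory parameters from normal to abnormal, based on Boston Children’s Hospital reference ranges". No matching sentence exists for vital signs.

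**The concern.** The endpoint asks how many children had an abnormal blood pressure, pulse, respiratory rate or temperature. The assigned analysis describes the average level of each sign and its average ratio to baseline. These are different quantities, and the first cannot be recovered from the second. Laboratory values have the same kind of endpoint and do get a matching count, so the gap is specific to vital signs.

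This is one of three safety endpoints listed in section 3.3.3 of an uncontrolled trial in children. Section 3.2.1 requires a central venous catheter, and sections 3.1 and 5.0 allow parenteral nutrition to be adjusted with attention to hydration and fluid balance. Section 10.2.3 also sends this vital-sign presentation to the DSMB. An analyst who followed the section literally would report vital signs without the stated incidence.

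**Working it through.** **1. Endpoint against analysis**

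| Item | Vital signs | Laboratory values |
|---|---|---|
| Endpoint (3.3.3) | Subject incidence of abnormalities | Subject incidence of abnormalities |
| Continuous presentation (10.2.3) | Yes | Yes |
| Count of abnormalities (10.2.3) | Not stated | Stated, against hospital reference ranges |

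**2. The plan's own precision for a proportion (section 10.2.5).** With n = 32 and p ± 1.96 × √(p(1 − p)/32):
- p = 0.20: 0.20 ± 0.139 = 0.061 to 0.339 (plan: 0.06 to 0.34)
- p = 0.50: 0.50 ± 0.173 = 0.327 to 0.673 (plan: 0.33 to 0.67)
- p = 0.80: 0.80 ± 0.139 = 0.661 to 0.939 (plan: 0.66 to 0.94)

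The figures reproduce. An incidence in 32 children is therefore something the plan already knows how to report.

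**3. Weight of each clinic visit in AUC7-90.** The formula in section 10.2.2 is the trapezoid sum divided by 90 − 7 = 83 days. Each visit's weight is half the adjoining intervals divided by 83.

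| Day | Weight | One child's AUC after a 40% rise at that visit only |
|---|---|---|
| 7 | 3.5/83 = 0.042 | 1 + 0.4 × 0.042 = 1.017 |
| 14 | 10.5/83 = 0.127 | 1.051 |
| 28 | 23/83 = 0.277 | 1.111 |
| 60 | 31/83 = 0.373 | 1.149 |
| 90 | 15/83 = 0.181 | 1.072 |

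The 40% rise is an assumption for illustration. The same deviation gives anything from 1.017 to 1.149, depending only on the visit at which it falls.

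**4. From one child to the group.** If 8 of 32 children (25%) had that rise at Day 7 only, the mean AUC would be 1 + (8/32) × 0.4 × 0.042 = 1.004. If it fell at Day 28 it would be 1 + (8/32) × 0.4 × 0.277 = 1.028. The incidence is 25% in both cases.

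**5. Cancellation.** A 40% rise at Day 28 is offset by a fall at Day 60 of 0.4 × 23/31 = 29.7%. The child's AUC is then exactly 1.000, the value that section 10.2.2 takes as no change.

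**6. A brief fever (assumed 37.0 °C at baseline, 39.5 °C at one visit).** The ratio is 39.5/37.0 = 1.068. The child's AUC runs from 1 + 0.068 × 0.042 = 1.003 (Day 7) to 1 + 0.068 × 0.373 = 1.025 (Day 60). The 32-child mean moves by at most 0.025/32, less than 0.001.

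**7. Abnormal at baseline.** A sign that is abnormal on Day 1 and unchanged has a ratio of 1 throughout, so the AUC cannot show it.

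**8. What the count would give.** For 0, 4 and 8 affected children of 32 (illustrative), the exact 95% intervals are 0% (0 to 10.9%), 12.5% (3.5 to 29.0%) and 25% (11.5 to 43.4%).

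**The case against.** Several points on the other side have force.

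- **A general rule for proportions exists.** Section 10.2.5 says dichotomous outcomes are presented as proportions, and having an abnormal sign or not is dichotomous. The exception list in section 10.2.2 is also incomplete: it omits laboratory abnormalities, which section 10.2.3 does count. So an intention to count vital-sign abnormalities can be argued. It remains an argument, because the one sentence about vital signs sends them to the continuous presentation, and the count that follows leaves them out.
- **The AUC may not be meant.** Section 10.2.3 says vital signs are presented like continuous outcomes, which could mean visit summaries alone. That is possible, and steps 3 to 7 of the working then do not apply. The endpoint still has no count.
- **Extreme values would be visible.** A reader might infer that a fever would vanish from the report. The documents do not support that: a temperature of 39.5 °C would appear as the visit maximum or in a by-subject display under section 10.2.1. But a pooled maximum across ages 2 to 18 gives no number of affected children, and only anthropometry is put on an age-standardised scale.
- **Adverse events give another route.** Section 9.1 counts an unfavourable sign as an adverse event, caregivers record events daily, and events of grade 2 or higher are tabulated by subject. So it would be wrong to say that abnormal signs have no count-based route. Events below grade 2 are not presented, however, and adverse events are a separate endpoint. Five clinic visits would also miss most brief episodes, so adverse-event reporting remains the better way to detect them.
- **Detail may sit in an SAP.** Numerical limits for an abnormal sign may properly be set there, and their absence from the protocol is not the fault.

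**Conclusion.** The point holds as a mismatch between a stated endpoint and its stated analysis. Section 3.3.3 promises a subject incidence of vital-sign abnormalities; section 10.2.3, read with section 10.2.2, assigns a presentation that does not estimate it. An SAP that followed those sections would inherit the gap.

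The size is modest. One of three safety endpoints would go unreported in the form named. Data collection, adverse-event reporting and the efficacy conclusions are unaffected. The conclusion about the missing count rests on the text alone. The AUC figures rest on the assumed deviations and on reading section 10.2.3 as including the AUC; they show only that the AUC cannot stand in for the count.

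A stronger reading, that the plan would conceal abnormal vital signs or that the AUC must be removed, is not supported. Listings, visit extremes and adverse-event tables remain, and adding the count is enough.

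**What to change.** Extend the incidence sentence in section 10.2.3, and its copy in the synopsis, to vital signs. For each sign, report how many treated children, and what percentage, had one or more abnormal values after baseline, with a table of shifts from baseline. State that abnormality is judged against age-appropriate limits fixed before database lock. The source of those limits has to be named, because the hospital reference ranges in the protocol are tied to laboratory values only. Name vital-sign incidence among the exceptions in section 10.2.2, and keep the continuous summaries as supporting description.

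The cost is a short wording change and one extra table. Vital signs are already taken on Day 1 and at every clinic visit, so no new data are needed.
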